# Potential of FX06 to prevent disease progression in hospitalized non-intubated COVID-19 patients — the randomized, EU-wide, placebo-controlled, phase II study design of IXION

**DOI:** 10.1186/s13063-022-06609-x

**Published:** 2022-08-19

**Keywords:** FX06, COVID-19, Disease progression, Capillary leak, Inflammation

## Abstract

**Background:**

More than 2.7 million hospitalizations of COVID-19-infected patients have occurred in Europe alone since the outbreak of the coronavirus in 2020. Interventions against SARS-CoV-2 are still in high need to prevent admissions to ICUs worldwide. FX06, a naturally occurring peptide in humans and other mammals, has the potential to reduce capillary leak by improving endothelial dysfunction and thus preventing the deterioration of patients. With IXION, we want to investigate the potential of FX06 to prevent disease progression in hospitalized, non-intubated COVID-19 patients.

**Methods:**

IXION is an EU-wide, multicentre, placebo-controlled, double-blinded, parallel, randomized (2:1) phase II clinical study. Patient recruitment will start in September 2022 (to Q2/2023) in Germany, Italy, Lithuania, Spain, Romania, Portugal, and France. A total of 306 hospitalized patients (≥ 18 years and < 75 years) with a positive SARS-CoV-2 PCR test and a COVID-19 severity of 4–6 according to the WHO scale will be enrolled. After randomization to FX06 or placebo, patients will be assessed until day 28 (and followed up until day 60). FX06 (2 × 200 mg per day) or placebo will be administered intravenously for 5 consecutive days. The primary endpoint is to demonstrate a difference in the proportion of patients with progressed/worsened disease state in patients receiving FX06 compared to patients receiving placebo. Secondary endpoints are lung function, oxygen saturation and breathing rate, systemic inflammation, survival, capillary refill time, duration of hospital stay, and drug accountability.

**Discussion:**

With IXION, the multidisciplinary consortium aims to deliver a new therapy in addition to standard care against SARS-CoV-2 for the clinical management of COVID-19 during mild and moderate stages. Potential limitations might refer to a lack of recruiting and drop-out due to various possible protocol violations. While we controlled for drop-outs in the same size estimation, recruitment problems may be subject to external problems difficult to control for.

**Trial registration:**

EudraCT 2021-005059-35. Registered on 12 December 2021. Study Code TMP-2204-2021-47.

**Supplementary Information:**

The online version contains supplementary material available at 10.1186/s13063-022-06609-x.

## Background

### Setting

SARS-CoV-2, officially referred to as severe acute respiratory syndrome-coronavirus-2 (SARS-CoV-2), has created an unknown challenge for healthcare systems worldwide. The virus was rapidly transmitted across geographic regions and triggered a pandemic due to the high infectivity, the ability to be spread even during the period of asymptomatic disease, and comparatively low virulence [1]. On December 8, 2019, the first case of the coronavirus disease 2019 (COVID-19) presented itself in the Hubei province of China [2]. Since then, the infection has spread worldwide, with nearly 433 million confirmed cases and 6 million deaths (World Health Organization situation report from March 8, 2022) [3].

The predominant clinical symptoms of COVID-19 are respiratory involvement, ranging from mild flulike illness to potentially fatal acute respiratory distress syndrome or fulminant pneumonia [1]. SARS-CoV-2 shares similar features with other coronaviruses, including the spherical morphology with spike projections on the surface as well as a high sequence identity, e.g. with SARS-CoV and SARS-like coronavirus (SL-CoV) [4]. In contrast to SARS-CoV, SARS-CoV-2 is less pathogenic but has a higher human-to-human transmissibility [5].

After SARS-CoV-2 infection, severe alveolar damage has been observed, which might be due to alveolar cells of the lung (type II) being more apt to be infected by SARS-CoV-2 [6]. SARS-CoV-2 infects host cells via angiotensin-converting enzyme 2 (ACE2) as its cellular receptor. This membrane-bound aminopeptidase receptor is predominantly expressed in humans in various tissues such as the heart, intestine, kidney, pulmonary alveolar cells, and ubiquitously on endothelial cells [7]. ACE2 counteracts the activity of angiotensin II and protects against harmful activation of the ACE system. It has been speculated that ACE inhibitors and angiotensin-receptor blockers (ARBs) may enhance ACE2 expression, thus predisposing to more severely COVID-19 progression [8]. SARS-CoV-2 has been shown to be capable of direct entry into engineered human blood vessel organoids in vitro [9]. The systemic impairment of microcirculatory function in various vascular beds might be explained by SARS-CoV-2-induced endotheliitis, which might also contribute to the clinically disastrous course of patients with severe COVID-19 [10].

The medication administered to patients, especially those with moderate to severe COVID-19, depends on the underlying pathologic features and the different clinical phases of the disease. Antiviral drugs (e.g. remdesivir), antiinflammation agents (e.g. dexamethasone), plasma, and hyperimmune immunoglobulins are part of the therapeutic options against COVID-19 [11]. Additionally, an emergency use authorization for combinational use of bamlanivimab and etesevimab for adult and pediatric SARS-CoV-2-positive patients with mild to moderate COVID-19, who are at risk of developing severe COVID-19, was granted by the FDA [12]. Approved uses include treatment of individuals aged 65 years or older and/or suffering from certain chronic diseases. Treatment with bamlanivimab and etesevimab is not authorized for patients hospitalized or receiving oxygen in context of a SARS-CoV2 infection, because the respective data are not available. Moreover, the delivery of monoclonal antibodies such as bamlanivimab and etesevimab to hospitalized COVID-19 patients in need of high flow oxygen or mechanical ventilation may be related to worse clinical outcomes [12].

This offers a justification for treatments stabilizing the endothelium with anti-inflammatory drugs such as anti-cytokine directed drugs like tocilizumab. A severe cytokine storm as caused by COVID-19 is followed by oedema, capillary leakage syndrome, and consequently dysfunction of the lungs and other organs [13].

There is still a lack of therapeutical options and a high medical need for efficacious and safe therapies for patients with COVID-19.

FX06, a naturally occurring peptide, might be an innovative promising strategy to improve endothelial dysfunction, capillary leak, arterial oxygenation, and lung function and possibly be able to prevent disease progression.

In a case report, FX06 was used to reduce capillary leak syndrome and to improve lung function in a patient with Ebola infection. FX06 administration led to a substantial improvement of the vascular leak syndrome and respiratory parameters. Additionally, the detection of Ebola-virus-specific antibodies was accompanied by a decrease in viral load [14].

In two German tertiary care university hospitals, six COVID-19 patients who suffered from moderate to severe ARDS at ICU admission and were mechanically ventilated were treated with i.v. FX06 (400–600 mg per day; 3–7 days) as part of an elective rescue treatment of seriously ill COVID-19 patients [15]. Patients were between 51 and 78 years of age; all had at least one comorbidity (e.g. obesity, type 2 diabetes mellitus, bronchial asthma) and all patients needed invasive ventilation. In the course of their disease, five out of these six patients required additional ECMO treatment. In the first 3 days after the start of FX06 administration, the mean oxygenation ratio improved, returned to baseline, and then increased steadily thereafter from the seventh day.

In a phase II study, 234 patients with acute myocardial infarction received FX06 in a dosage of 400 mg intravenously separated into two bolus injections in a 10-min interval. The therapy with FX06 showed a significant reduction of the necrosis zone 5 days after the event, evaluated by MRI. Patients treated with FX06 also showed a trend towards improvement of a combined clinical endpoint of mortality and any cardiac event. Numerically less serious cardiac events occurred in the FX06-treated group than in the placebo group, and there were no differences in adverse events [16].

FX06 might be an innovative promising strategy to improve endothelial dysfunction, capillary leak, arterial oxygenation, and lung function possibly able to prevent disease progression.

## Methods

The study was planned in concordance with the SPIRIT statement guideline to ensure complete reporting of the study [17]. Study protocol V1.1 (EudraCT no. 2021-005059-35), patient information, and informed consent were approved by the Ethics Committee of the University of Frankfurt, Germany (Ref: 2021-512-AMG, Chair: [name]. [name]) and of all participating centres on 18 February 2022. At the same time, the study documents have been approved by the responsible federal authority (Bundesinstitut für Arzneimittel und Medizinprodukte – No. 61-3910-4045190) according to the requirements of §42 Abs. 2 AMG and §9 GCP-V. Each patient must give written informed consent to participate in the study.

Protocol modifications to ongoing studies must be made via amendment and they will be communicated via the EU. The sponsor is responsible to obtain independent approval for the amendment from the federal regulatory authority and a positive opinion from the competent ethics committees if required according to GCP. If applicable, regulatory authority must be notified about the amendment. The sponsor will prepare a complete, integrated final clinical study report of the study. This report will be signed by the coordinating investigator of the study. The investigator/investigator(s) will each receive a copy of this report.

Publication(s) will be prepared according to standard guidelines, authorships are determined internally and according to authorship guidelines (e.g. Good Publication Practice and Recommendations for the Conduct, Reporting, Editing, and Publication of Scholarly Work in Medical Journals).

### Trial design

IXION will be an EU-wide, multinational, placebo-controlled, double-blinded, parallel, randomized (2:1), phase II clinical study to investigate the superiority of FX06 compared to standard of care to prevent disease progression in hospitalized non-intubated COVID-19 patients. In total, 306 patients fulfilling inclusion criteria will be stratified according to their WHO severity group (moderate: score 4–5 or severe: score 6) and by centre and randomized 2:1 to either one of the two treatment groups (FX06 or placebo) (Fig. 1).

**Fig. 1 Fig1:**
[figure not shown]
Study design of IXION. Hospitalized, non-intubated COVID-19 patients will be included in this study and stratified by WHO score. Patients will then be randomized 2:1 to either FX06 or placebo. FX06 or placebo will be administered intravenously for 5 consecutive days. Patients will be assessed and observed for 28 days and followed up until day 60. SCR screening, BL baseline, FU follow-up, i.v. intravenous, R randomization, WHO World Health Organization. *Day 2–27 will include personal visits as well as remote “visits”

**Table 1 Tab1:**
[figure not shown]
Timeline of IXION. Overview of assessments and time points of visits during the study period

^1^Screening and baseline should be maximally 5 days apart, but can also be performed at the same day; ^2^if patients are not in the hospital anymore, patients can be contacted remotely to retrieve the information; ^3^IMP administration will be performed at BL and the following 4 days; ^4^FU can be performed as a telephone call and will be performed at day 60; ^5^lung function parameters will only be documented if they are routinely measured; ^6^blood sample collection before first dose of IMP; ^7^only in women of childbearing potential; urine pregnancy test; ^8^to be administered as interview; ^9^WHO score will be eligible for the whole study period for evaluation of disease severity also if patients become SARS-CoV-2 negative during the study period; ^10^will be done in clinical routine by the local laboratory and will be documented for the study

Due to the multinational design, patients will be recruited in Germany, Italy, Lithuania, Spain, Romania, Portugal, and France.

### Participants

In this study, we will investigate the potential of FX06 to prevent COVID-19 progression in hospitalized, non-intubated COVID-19 patients. We will also investigate the influence on disease improvement, lung function, endothelial dysfunction, capillary leak, and arterial oxygenation in SARS-CoV-2 positive, hospitalized patients. Therefore, in this study, hospitalized, non-intubated COVID-19 patients will receive FX06 (in addition to standard of care (SoC)) or placebo (in addition to SoC) over 5 days. Patients will be observed until day 28 (and followed up at day 60) (Table 1).

Patients and potential study participants are identified by the study centres of the clinical partners and included in the study upon enrolment according to the following criteria:

### Inclusion criteria

SARS-CoV-2 infection confirmed by PCR testHospitalized patientsWHO scores 4–6Oxygen saturation ≤ 92% under room airBreathing frequency per minute ≥ 20Patients ≥ 18 years and < 75 yearsWritten informed consent obtained prior to the initiation of any protocol-required procedures by the patientWillingness to comply to study procedures and study protocolPatients able to understand the requirements of the study and give written informed consent

### Exclusion criteria

Significant underlying known comorbidities or conditions, defined as:Other severe advanced or chronic lung diseases (e.g. COPD Gold ≥ III, severe silicosis)End-stage chronic kidney disease (stage 5)End-stage chronic heart failure (NYHA ≥ III)DementiaBaseline neurologic disease which would preclude rehabilitation potentialDisseminated and/or metastasized malignancySevere deconditioning with a life expectancy of less than 6 months according to the treating physicianImmunocompromized patients:I.Recipient of a solid organ transplantII.Regular intake of anti-inflammatory therapy due to concomitant auto-immune disease (e.g. biologics)III.Primary immune deficiencyEvidence of other significant uncontrolled concomitant diseases or serious and/or uncontrolled diseases with a bad prognosis that are likely to interfere with the evaluation of the patient’s safety and with the study outcome as judged by the treating physicianWomen pregnant or breastfeedingMales or females of reproductive potential not willing to use effective contraception for the duration of the study periodCurrent participation in another interventional clinical trial with IMP or participation within the last 30 days

### Intervention trial drug — FX06

FX06 is a naturally occurring peptide in humans and mammals, Bβ15-42, derived from the E1 fragment of fibrin. The mechanism of action of FX06 is an important new discovery in understanding acute inflammation and oedema formation. FX06 competes with E1 fragments of fibrin for binding to an endothelial specific molecule, VE-cadherin, thereby acting as an anti-inflammatory, and it signals through VE-cadherin, thereby reducing plasma leakage into tissues [16, 18]. Based on animal models of vascular leakage and systemic inflammation, FX06 has considerable therapeutic potential for all diseases and pathological conditions associated with increased vascular permeability [19, 20]. FX06 binds to vascular endothelial (VE)-cadherin, preventing VE-cadherin-dependent transmigration of leukocytes [21]. Besides many different animal models of shock (septic, haemorrhagic, hypovolemic), FX06 was also tested in acute and chronic models of myocardial ischaemia and reperfusion injury in rats, mice and pigs [18] [20, 22]. FX06 reduced relative infarct size by more than 40%; this effect size is comparable to ischaemic preconditioning. The peptide is synthetically produced for exogenous human administration [21]. FX06 was well tolerated in the phase I study [21].

FX06 has been evaluated in a phase IIa clinical trial of first-time acute STEMI (ST-segment elevation myocardial infarction) patients undergoing primary percutaneous coronary intervention. In this proof-of-concept trial, FX06 reduced the necrotic core zone as one measure of infarct size on magnetic resonance imaging and appeared safe and well tolerated.

Furthermore, FX06 has been applied in a severe case of an Ebola virus-infected patient under compassionate use. The patient recovered after critical illness and no drug-related safety concerns were raised [21].

An investigator-initiated trial (IIT) in France treated mechanically ventilated patients with critical COVID-19 in a phase IIa study using the investigational product FX06/placebo (EudraCT no. 2020-002056-20).

Since there were no safety concerns in the phase II IIT study with FX06 in France/Paris, in which FX06 was administered intravenously for 5 days (2 × 200 mg per day), it was therefore decided to use the same dosage regimen.

### Randomization

A randomization list will be generated by an authorized person through the sponsor. Central randomization will be performed in a 2:1 allocation to FX06 and placebo stratified by WHO group (moderate: score 4–5 and severe: score 6) and centre. As randomization procedure, stratified block randomization will be applied. The randomization will be performed centrally within the eCRF System Open Clinica. Independent pharmacists will dispense the allocated treatment according to the computer-generated randomization list.

### Allocation

The randomization list is not available to blinded study staff including treating physicians. Within the clinics, treatment allocation will be concealed by providing placebo IMP for FX06, which will be of identical appearance in comparison to the study drug.

### Implementation

The randomization sequence is generated and validated prior to study start by the data management. Eligible patients are enrolled by the treating investigator who allocates the patients to the next randomized treatment according to the computer-generated randomization list. Blinded IMP is then given according to randomization number.

### Blinding

The study is randomized and blinded to subjects, therapists, and assessors (double-blinded). Treatment allocation remains concealed throughout the study, minimizing the risk of assessment and selection bias and assessment bias.

The treatment allocation also remains blinded for the study statistician until the final analysis to avoid early data-driven conclusions.

### Study objectives

#### Primary objective and endpoint

The primary objective is to demonstrate a difference in the proportion of patients with progressed/worsened disease state in patients receiving FX06 compared to patients receiving placebo until day 28.Proportion of patients with worsened disease state until day 28 in both treatment groups

Progression/worsening of disease state will be defined as a worsened WHO score on 3 consecutive days (always compared to the BL WHO score) until day 28 (e.g. a WHO score of 5 on 3 consecutive days for a patient that had a WHO score of 4 at BL will be defined as a worsened disease)

The assessment of disease severity and progression by the WHO score was chosen based on the recommendation of the WHO [23] to include this score for all COVID-19 clinical trials. Furthermore, for this international, multicentre study, it facilitates comparable and objective assessment of disease severity across study centres.

#### Secondary objectives and endpoints

Assessment and treatment comparison of the following objectives at all available visits and time points between the FX06 and placebo group:Disease progression/improvement (WHO scale score)Proportion of patients with improved or progressed disease stateProportion of patients with each WHO scoreAverage change in WHO score compared to BLAverage WHO scoreProportion of patients in each disease severity state (uninfected, mild, moderate, severe, dead)Proportion of patients who need mechanical ventilation and number of ventilation daysProportion of patients who need ECMO and number of days on ECMOLung function (partial oxygen pressure, fraction of inspired oxygen, Horowitz index)Absolute PaO2 (mmHg) values and change compared to BLAbsolute FiO2 (mmHg, fraction of inspired oxygen) and its change to BLHorowitz Index (mmHg) and change to BL*(Lung function assessments will only be documented for the study if routinely done)*Oxygen saturation and breathing rateOxygen saturation and breathing rate and change to BLProportion of patients reaching > 92% oxygen saturation under room airSystemic inflammation (changes and normalization in troponin, procalcitonin, CRP, leukocyte count, ferritin, D-dimers, lactate, lactate dehydrogenase, albumin)Concentration of blood parameters and their change to BLProportion of patients with normalized systemic inflammation (for each inflammation parameter)SurvivalProportion of patients who survived until day 28Proportion of patients who survived until day 60Capillary refill timeProportion of patients with normal and pathological capillary refill time at baseline (as pathological: ≥2 s or normal: <2 s) and change to BLDuration of hospital stayLength of hospital stay until day 28 or until day 60Proportion of patients that have been discharged from the hospital until day 28 and day 60Drug accountability (e.g. dose, number of administrations)Number of IMP administrationsMean IMP dose per day and mean cumulative IMP doseSARS-CoV-2 rRT-PCR ct values and time to negativity (i.e. two consecutive negative PCR-tests as defined by each local laboratory)Time to SARS-CoV-2 RT-PCR negativity in respiratory tract specimenProportion of patients with a negative SARS-CoV-2 PCR test at day 6, 10, and 28Change (reduction) in SARS-CoV ct valuesSubgroup analysis: Concomitant medication and SARS-CoV-2 vaccination status

We describe the subgroup analyses descriptively for the treatment groups. We also reserve the right to compare them between groups with exploratory statistical tests.

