#### Missing values

We do not expect many regular missing values due to the close visit windows and patient care. Collection of the WHO score up to day 28 will be tightly controlled for. In general, real missing data of a parameter will not be transformed and remains untouched unless stated otherwise. Summary statistics will be given including the underlying number of valid individual values and missing visit-wise.

We predefine the following measures for handling data of selected analyses:

All patients who die prior to day 28 will be given the corresponding highest WHO score (score of 10) for all remaining visits at and after assessment visit of their death for the purpose of assessing the primary endpoint and related sensitivity analyses even though no further patient data can be collected after visit of death. The date of death will be considered the time point for the time-to-event analyses. In case of drop-outs prior to day 28 or missing WHO scores of the FAS population prior to day 28 it will be evaluated, if a statistical deduction of the primary endpoint is possible independent of missing WHO scores, e.g. because the patient shows a worsened WHO score at some point, or no more than 3 consecutive visits show a worsened WHO score. If such a deduction of the primary endpoint is not possible, a decision on missing WHO scores may be deduced by taking a closer look at these cases at the blind data review meeting where all available information on the patient is evaluated in a blinded manner. All remaining patients of the FAS where no WHO score can be assigned will be considered missing for the primary analyses and will be considered by different scenarios as sensitivity analyses of the primary analysis (best/worse-case scenario and by LOCF). For all further endpoints, no imputation is planned currently.

Note that linear mixed models using maximum likelihood estimation are able to deal with missing values and are a valid alternative to imputation. As such, laboratory assessments are expected to be modelled accurately in terms of missing in LMMs.

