#### Statistical analyses

As primary analysis, we will compare the difference in proportion of patients with progressed/worsened disease state (as defined according to WHO score) until day 28 in both treatment groups (2-sample chi squared test). The aim is to demonstrate preliminary superiority of FX06 in prevention of worsened disease state in comparison to placebo (with standard of care) treatment. For the group comparison, the 5% significance level is considered.

With regard to secondary endpoints, these will be described by summary statistics stratified by treatment group and available visits and the treatment difference until day 28; the 95% confidence interval will be given. For selected secondary endpoints, linear mixed models will be applied to investigate the impact of treatment, time, treatment-by-time, and other factors such as demographics.

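### PaO2, FiO2 and Horowitz index are recorded only when routine care measures them, yet the arms are compared on whatever values exist, which tends to dilute a true benefit; the Ct endpoint needs its direction corrected and a rule for negative tests

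*Protocol article*

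**What the plan says.** The recording rule for lung function stands twice in the protocol article. The endpoint list has "Lung function assessments will only be documented for the study if routinely done", and a footnote to the visit schedule (Table 1) has "lung function parameters will only be documented if they are routinely measured".

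The heading sentence of the secondary endpoints nevertheless announces "Assessment and treatment comparison of the following objectives at all available visits and time points between the FX06 and placebo group". Absolute PaO2, FiO2 and Horowitz index, and their changes from baseline, are on that list. Under Statistical analyses, secondary endpoints get summary statistics by arm and visit, with a treatment difference up to day 28 and its 95% confidence interval. The same section adds "For selected secondary endpoints, linear mixed models will be applied", without naming the endpoints.

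Under Missing values, "real missing data of a parameter will not be transformed and remains untouched unless stated otherwise", and after the rules for the WHO score, "For all further endpoints, no imputation is planned currently". The general answer offered is that "linear mixed models using maximum likelihood estimation are able to deal with missing values and are a valid alternative to imputation". No condition is attached.

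For viral load, the endpoint list names change in Ct, with the word reduction in brackets. Time to PCR negativity and the proportion negative at days 6, 10 and 28 are separate endpoints. No value or rule for a negative test is attached to the Ct endpoint.

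**The concern.** Randomization balances the arms as randomized. It does not balance the subset in whom a clinician later chose to take a blood gas. That choice probably follows the patient's condition, and the schedule allows discharged patients to be contacted remotely, when a blood gas is unlikely. If FX06 keeps patients better, fewer FX06 patients will have values, and those who do will be the sicker ones. Comparing observed values then sets a selected part of one arm against a differently selected part of the other.

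The plan has nothing specific for this. The rule that scores death as 10, and the best-case, worst-case and LOCF scenarios, apply to the WHO score only. Likelihood-based mixed models are valid when missingness depends on data in the model. A blood gas omitted because the patient looked well that day may not meet this condition.

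The Ct endpoint has a related gap. A negative test ordinarily yields no Ct value, so patients who clear the virus may drop out of a comparison of observed values. The bracketed word also points the wrong way, because Ct rises as viral load falls.

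Oxygenation and lung function are named targets of the drug in the Background and Participants sections. A weak or absent difference here could be read as evidence against the mechanism when it partly reflects who was measured.

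**Working it through.** **What the documents supply.** They give the recording rule, the between-arm comparison, the absence of imputation and the unconditional mixed-model statement. They do not say how often blood gases are taken, how measurement relates to condition, or the mean or SD of Horowitz index or Ct. There is no figure of the plan's own to reproduce on this point, and every number below is an assumption chosen to show the range.

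**Graded selection, Horowitz index.** Assume a normal distribution with placebo mean 200 mmHg and SD 80. The probability of being measured is 1/(1 + exp(b(x − 200)/80)), so half the placebo arm is measured and sicker patients are measured more often as b grows. The observed difference is the mean of measured FX06 values minus the mean of measured placebo values:

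| b | true 0 | true 20 | true 40 | FX06 measured if true 40 (placebo 50%) |
|---|---|---|---|---|
| 0 | 0 | 20 | 40 | 50% |
| 0.5 | 0 | 18.9 | 37.8 | 44% |
| 1 | 0 | 16.6 | 33.1 | 40% |
| 2 | 0 | 12.5 | 24.6 | 35% |

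**Hard cut-off, Horowitz index (the severe case).** Assume means 200 and 220, SD 70, with everyone below a cut-off c measured and nobody above it. Then E[X | X < c] = μ − σ·φ(a)/Φ(a), with a = (c − μ)/σ.

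- c = 250: placebo 200 − 70 × 0.3091/0.7625 = 171.6; FX06 220 − 70 × 0.3639/0.6659 = 181.7; difference 10.1.
- c = 200: placebo 200 − 70 × 0.3989/0.5000 = 144.1; FX06 220 − 70 × 0.3830/0.3875 = 150.8; difference 6.7.
- c = 150: placebo 200 − 70 × 0.3091/0.2375 = 108.9; FX06 220 − 70 × 0.2420/0.1587 = 113.2; difference 4.3.

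The true difference is 20 in all three.

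**Ct.** Assume placebo mean 35, SD 5, and no value at 40 or above. By the same formula the placebo mean among observed values is 35 − 5 × 0.2420/0.8413 = 33.56.

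- True shift +2: 37 − 5 × 0.3332/0.7257 = 34.70, so +1.1 is observed, with 73% of FX06 and 84% of placebo patients still having a value.
- True shift +4: 39 − 5 × 0.3910/0.5793 = 35.62, so +2.1 is observed, with 58% against 84%.

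**Reading.** In every scenario in which measurement depends on condition, a true benefit shrinks. With no true effect, the difference stays at zero.

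**The case against.** The strongest case against runs as follows.

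- **Blinding.** The trial is double-blind, so knowledge of the arm cannot drive measurement, and there is no bias under no effect. This stands. It rules out a spurious benefit arising from measurement under the null, but does not prevent dilution of a real effect.
- **Size.** Under mild to moderate graded selection a true 20 mmHg loses only about 1 to 3 mmHg. The hard cut-off is a worst case and should not be quoted alone. This stands too.
- **Existing safeguards.** The Missing values section already promises counts of valid and missing values by visit, and SpO2, breathing rate and WHO score are already secondary endpoints. That is correct. What remains is the treatment difference with a confidence interval on the selected values.
- **Mixed models.** A reader might infer that a mixed-model test of Horowitz index is planned. The text does not say so: the models are for unnamed endpoints, and the confident remark about accurate modelling concerns laboratory assessments. Nor is it shown that the models fail. If values already observed and in the model explain why measurement stops, they can remain valid. The fault is that the condition is not stated.
- **Ct.** A reader might infer that patients who turn negative certainly leave the analysis and that viral clearance is hidden. The documents do not support this. The generic rule for values beyond the limit of quantification could be read to cover a negative test, and PCR negativity is analysed separately. However, that rule does not name Ct and lists zero among the possible fixed values, which would make no sense for Ct. No directional Ct test is stated, so the bracketed word is a wording error and does not show that a result will be misread.

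**Conclusion.** The concern holds for PaO2, FiO2 and Horowitz index. The plan compares the arms on values whose existence probably depends on condition after randomization, with no imputation and no stated condition for the model-based alternative. The likely consequence is dilution of a true benefit. That blood gases are taken more often in sicker patients is plausible, but the article does not state it.

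The size cannot be fixed from the documents. Under the assumptions shown, a true 20 mmHg appears as about 12 to 19 with graded selection and about 4 to 10 with a hard cut-off. A reader might infer that the trial's conclusions are biased generally. They are not: the primary endpoint and the sample size are unaffected.

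The Ct part is weaker. It comes down to a wrong direction word and the lack of a rule for negative tests, softened by the separate negativity endpoints.

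**What to change.** 1. Label PaO2, FiO2 and Horowitz index as descriptive. Give the number measured per arm and visit, and make no inferential treatment comparison.
2. Base the between-arm oxygenation comparison on WHO score, and on SpO2 and breathing rate, which do not carry the routine-care restriction. Report the completeness of SpO2 and breathing rate by arm and visit: the schedule table is not shown and visits may be remote, so full collection cannot be assumed.
3. In Missing values, state that mixed models are valid only if data are missing at random, and add a missing-not-at-random sensitivity analysis wherever they are used.
4. For Ct, drop the bracketed word and state that an increase is the favourable direction. Analyse negative tests as right-censored at the assay's cycle limit, instead of leaving them missing or applying the generic quantification-limit rule.

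The cost is a change of endpoint and analysis wording, slightly more analysis work, and no formal comparison on Horowitz index. No new measurements are needed.
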